## Abstract

**Background:**

Preterm newborns can be exposed early to significant perinatal stress, and this stress can increase the risk of altered socioemotional development. Sustained social withdrawal in infants is an early indicator of emotional distress which is expressed by low reactivity to the environment, and if persistent, is frequently associated with altered psychological development. Infants born prematurely have a higher probability of developing sustained social withdrawal (adjusted odds ratio 1.84, 95% CI 1.04-3.26) than infants born full term, and there is a correlation between weight at birth and sustained social withdrawal at 12 months of age.

**Objective:**

The aims of this study are to compare the effect of the interactive guidance intervention to that of routine pediatric care on sustained social withdrawal in infants born moderately or late preterm and to explore the relationship between sustained social withdrawal in these infants and factors such as neonatal intensive care unit hospitalization variables, parental depression, and posttraumatic stress symptoms.

**Methods:**

This study is designed as a multicenter randomized controlled trial. Moderate and late preterm newborns and their parents were recruited and randomized (1:1 allocation ratio) to control and experimental groups. During neonatal intensive care unit hospitalization, daily duration of skin-to-skin contact, breastfeeding, and parental visits were recorded. Also, a daily score for neonatal pain and painful invasive procedures were recorded. After discharge from neonatal intensive care, for the duration of the study, both groups will attend follow-up consultations with neonatologists at 2, 6, and 12 months of age (corrected for gestational age) and will receive routine pediatric care. Every consultation will be recorded and assessed with the Alarm Distress Baby Scale to detect sustained social withdrawal (indicated by a score of 5 or higher). The neonatologists will perform an interactive guidance intervention if an infant in the intervention group exhibits sustained social withdrawal. In each follow-up consultation, parents will fill out the Edinburgh Postnatal Depression Scale, the modified Perinatal Posttraumatic Stress Disorder Questionnaire, and the Impact of Event Scale–revised.

**Results:**

Recruitment for this trial started in September 2017. As of May 2020, we have completed enrollment (N=110 infants born moderately or late preterm). We aim to publish the results by mid-2021.

**Conclusions:**

This is the first randomized controlled trial with a sample of infants born moderately or late preterm infants who will attend pediatric follow-up consultations during their first year (corrected for gestational age at birth) with neonatologists trained in the Alarm Distress Baby Scale and who will receive this interactive guidance intervention. If successful, this early intervention will show significant potential to be implemented in both public and private health care, given its low cost of training staff and that the intervention takes place during routine pediatric follow-up.

**Trial Registration:**

ClinicalTrials.gov NCT03212547; https://clinicaltrials.gov/ct2/show/NCT03212547.

**International Registered Report Identifier (IRRID):**

DERR1-10.2196/17943

## Introduction

### Background

In infants in the normal range of development, skills to engage with caregivers such as initiating and maintaining eye contact, vocalizing, using facial expressions, and using body movements, emerge during the first two months after birth [1,2]. The level of synchronization between infants and their caregivers and the capacity of caregivers to detect interactive errors and attune with the infant’s emotional state and interactive behaviors appears to be critical for optimal psychological development in the first 18 months of life [3].

Infants can display social withdrawal behaviors as a reaction to minor transient perturbations when interacting with caregivers or when agitated or tired; however, infants are usually able to reengage as soon as they regain the full attention of the caregivers [4-6]. In contrast with this adaptive social withdrawal behavior, sustained social withdrawal is significantly less common and reflects a sustained decrease in engagement during interactions and a sustained decrease in reactivity to the environment [7,8]. Sustained social withdrawal can be assessed by the Alarm Distress Baby Scale [9] and is defined by a score of 5 or higher. Persistent (both repetitive and accumulated) sustained social withdrawal has been shown to be a risk factor for altered emotional development in infants [10].

Sustained social withdrawal has typically been associated with severe pathological conditions in infancy such as posttraumatic stress disorder [4], autism spectrum disorders [11], and child depression [12]. Infants demonstrating sustained social withdrawal have a higher risk of developing attachment disorders [13], emotional or behavioral disorders [14], motor and language delays [15], and altered interactive skills [10,16]. Sustained social withdrawal has also been linked with medical conditions such as intrauterine growth retardation, preterm birth [17], early cardiac surgery [18], Prader-Willi syndrome [19], and cleft lip and palate [20], as well as factors in family medical history such as both parents having mental health problems [2]. Sustained social withdrawal has proven to be an important indicator of infant distress regardless of the cause [10].

The Alarm Distress Baby Scale is a well-validated screening tool designed to assess sustained social withdrawal in infants between 2 and 24 months of age in primary care settings such as routine medical checkups or testing [21]. The infant can be assessed during the interaction with the medical professional which avoids putting pressure on the parents (because of their perception that it reflects their caregiving competence) [22].

### Preterm Infants and Mental Health Developmental Risk

Infants born preterm often spend their first days, weeks, or even months in a neonatal intensive care unit where they undergo numerous painful and invasive procedures [23] and can be submitted to various perinatal stresses. During this period, in which both the development and the life of the neonatal infant can be at risk, the infants and their families must adapt to health care unit protocols with respect to visits and care. In addition, the mental health of the parents may be affected increasing the risk of posttraumatic stress and postpartum depression [24].

Several studies have shown that the prevalence of psychopathologies appeared to be significantly higher in infants born preterm than in infants born full term. So far, most studies have focused on infants born very prematurely and have shown high prevalence of autistic spectrum disorders [25], attention-deficit and hyperactivity disorders [26], attachment disorders [13], emotional problems [27], and social withdrawal behavior [28] and growing recognition of behavioral problems [29], lower socioemotional competence [30], and developmental delay [31] relative to prevalence of these in infants born moderately and late preterm. Furthermore, associations between late preterm birth and poor socioeconomic outcomes in adulthood [32] and late preterm birth and poor neurocognitive functioning in late adulthood [33] have been described.

In their first year (corrected for gestational age), infants born preterm have a higher probability of developing sustained social withdrawal (adjusted odds ratio 1.84, 95% CI 1.04-3.26) when compared to that of infants born full term [17] (prevalence was 22.1% and 13.9% for infants born preterm and born full term, respectively). Other studies have found prevalences of sustained social withdrawal that vary from 11.3% to 22.1% for infants born preterm [6,13,17,34].

### Chilean Preterm Infants: Early Detection and Intervention

In Chile, preterm birth rates have been increasing over the last decade. In 2016, 8.3% of live births were preterm (gestational age less than 37 weeks) [35]. Neonatal medical care is provided for these infants (if needed) by a national network of 29 neonatal intensive care units, and follow-up care is provided by interdisciplinary teams in 35 preterm polyclinics. Within the public health system in Chile, all preterm infants are assessed with the Psychomotor Development Assessment Scale [36] between the ages of 0 and 2 years.

Since intervention becomes more challenging as problems in infancy grow more complex or more severe [37], assessing the effectiveness of early sustained social withdrawal detection in preterm infants (using the Alarm Distress Baby Scale) as a precursor to early intervention appears to be an interesting goal.

The Alarm Distress Baby Scale [9] can be used as early as two months of age (corrected age in the case of infants born preterm) and has demonstrated acceptable levels of specificity and sensitivity in several studies (reported in a review study) [10]. In a study with full-term infants, Bonifacino et al [38,39] described a significant difference in sustained social withdrawal in the infants who were followed by Alarm Distress Baby Scale–trained pediatricians compared to sustained social withdrawal in infants who attended routine pediatric follow-up care. Facchini et al [40] investigated the feasibility of a feedback guidance intervention performed by Alarm Distress Baby Scale–trained pediatricians on infants born full term at public well-baby clinics in Italy, and they concluded that these interventions are easily implemented and accepted by patients and their families; however, to the best of our knowledge, there are no reports regarding the effect of an interactive guidance intervention performed by Alarm Distress Baby Scale–trained neonatologists on infants born moderately or late preterm during their first twelve months (corrected age).

The main objective of this study is to compare the effect of an interactive guidance intervention on sustained social withdrawal scores in infants born moderately or late preterm compared to those of infants born moderately or late preterm in routine pediatric care.

## Methods

### Study Design

The study is designed as a randomized controlled trial (NCT03212547), in order to remove bias in treatment allocation and the effect of possible confounding variables [41]. Chilean infants who were born moderately preterm or late preterm (up to N=110) and their parents will be included and randomized in a 1:1 allocation ratio to an intervention group (up to n=55) and a control group (up to n=55). Both groups will receive routine pediatric care at medical checkups at 2, 6, and 12 months of age. All ages used in this study refer to corrected age. To calculate corrected age, the difference in weeks of gestation at the time of birth and full term (40 weeks of gestation) is subtracted from the infant’s chronological age. In addition, the intervention group will receive the interactive guidance intervention, performed by Alarm Distress Baby Scale–trained neonatologists, if the neonatologists detect sustained social withdrawal (a score of 5 or higher in the Alarm Distress Baby Scale) during the routine medical checkups. The interactive guidance intervention will follow a standardized protocol designed by the research team before the start of the recruitment. The control group will not receive the interactive guidance intervention during the first 12 months; however, if any infant in the study receives a score of 5 or higher on the Alarm Distress Baby Scale at the 12-month checkup, they will be offered further assessment and intervention.

### Inclusion Criteria

Only preterm infants born from single or twin pregnancy (monochorionic or dichorionic), born between 32 weeks 0 days and 36 weeks 6 days gestation (as determined by neonatologist), hospitalized within the first 48 hours after birth, and remaining at least 48 hours in the neonatal intensive care unit were eligible to participate in this study. Parents of the infants were required to be Spanish speaking and have stable living arrangements to ensure the effectiveness of the interactive guidance intervention (carried out by Spanish-speaking neonatologists). Parents of infants born preterm were recruited from two neonatal intensive care units—Clinica Alemana de Santiago and Hospital San Jose—by a principal investigator or co-investigator of the study or by the neonatal study coordinator. Clinica Alemana de Santiago is a private health center located in a district of Santiago, Chile with a poverty rate of 0.1% whereas Hospital San Jose is a public health center located in a district of Santiago, Chile with a poverty rate of 8.2% [42,43]. At enrollment, socioeconomic variables were recorded using a socioeconomic survey, and pregnancy and postpartum variables were recorded using a perinatal background questionnaire.

### Exclusion Criteria

Infants were not eligible for participation in this study if their mother had history of or confirmed exposure to cocaine, marijuana, or other illicit mind-altering substances during pregnancy; if the infant had a neurological disease that impairs development that was confirmed at birth; if the infant had major congenital malformations, suspected or confirmed genetic disorders; and if perinatal asphyxia occurred at birth (defined as an Apgar score less than 3 at 1 minute or an Apgar score less than 5 at 5 minutes, or cord pH less than 7.0 at birth).

### Protocol

For this study, in 2017, Bonifacino et al [38] conducted Alarm Distress Baby Scale training in Chile over 4 days which consisted of 30 hours and 12 training modules. The program featured 2 central theoretical modules which covered early interactions and emotional development, emotional deprivation and its consequences, social withdrawal behaviors as an early alarm sign, and the Alarm Distress Baby Scale fundamentals. Subsequently, 10 modules of video training were presented featuring material with infants between 2 and 24 months of age. These infants had attended medical checkups with Alarm Distress Baby Scale–trained and untrained pediatricians. Following the videos, there was an exam to certify the professionals in the use of the Alarm Distress Baby Scale. Fleiss kappa was used to determine if there was agreement between the 11 evaluators regarding diagnosis (normal behavior or sustained social withdrawal). There was a substantial agreement [44] between evaluators (κ=0.794, 95% CI 0.676-0.913; *P*˂.001). Individual kappa values for normal and sustained social withdrawal categories were κ=0.795 and κ=0.794, respectively.

One fundamental element of the training was that the professionals learned not only to detect the sustained social withdrawal behaviors (and to score these behaviors using the Alarm Distress Baby Scale), but also to meaningfully show the parents how—in terms of communication or contact—their infants seek interaction, with the objective of reducing sustained social withdrawal behaviors.

Participants of the study will be recruited during their admission to the neonatal intensive care units by members of the researcher team and enrolled and randomized by a study coordinator to either the intervention or the control group. The infant will be randomized in a 1:1 allocation using SPSS Statistics (version 25.0; IBM Corp), stratified by hospital center (Clinica Alemana de Santiago or Hospital San Jose) in blocks of four. Also, infants will be stratified into two groups, single or twin pregnancy, in order to isolate the intervention effect from that of other covariables (such as mother of twins learning). The Hospital San Jose sample will also be stratified into two groups, whether the infant is included or is not included in the Kangaroo Care program, since only Hospital San Jose currently offers this program that aims to promote mother infant bonding, and which could potentially act as a confounding variable.

As shown in Figure 1, all infants will receive routine pediatric care during the medical checkups at 2, 6, and 12 months of age, but in addition, infants in the intervention group will also receive the interactive guidance intervention if the Alarm Distress Baby Scale–trained neonatologists detect sustained social withdrawal during these medical checkups. All medical checkups will be video-recorded, and the videos will be assessed by external Alarm Distress Baby Scale–trained evaluators, and at every medical checkup, parents will fill out the Edinburgh Postnatal Depression Scale, the modified Perinatal Posttraumatic Stress Disorder Questionnaire, and the Impact of Event Scale–revised.

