### Statistical Analysis

Two-tailed paired *t* tests will be used to compare covariates and dependent variables from the infant groups. A one-way analysis of covariance will be used to determine the effects of covariates (sociodemographic and neonatal intensive care unit hospitalization variables, postpartum depression, and posttraumatic stress) on the comparisons between groups (control and intervention) and between times (2, 6, and 12 months of corrected age medical checkups) regarding the dependent variable (sustained social withdrawal). Other statistical techniques such as matching, odds ratios, and logistic regression will also be used.

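### Randomisation is stratified by centre, single or twin pregnancy and Kangaroo Care, but the stated analysis does not name these factors; if they are prognostic, the linear model's standard error comes out too large and some power is lost

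*Protocol article*

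**What the plan says.** Under Methods, the section headed Protocol sets three stratification factors. Allocation is 1:1 and "stratified by hospital center (Clinica Alemana de Santiago or Hospital San Jose) in blocks of four". Next, "infants will be stratified into two groups, single or twin pregnancy, in order to isolate the intervention effect from that of other covariables", with learning by mothers of twins given as the example. Finally, "The Hospital San Jose sample will also be stratified into two groups, whether the infant is included or is not included in the Kangaroo Care" programme, because only that hospital offers it and it might confound. No reason is given for stratifying by centre, but Inclusion Criteria contrasts a private centre in a district with 0.1% poverty and a public one in a district with 8.2%.

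The Statistical Analysis section names three kinds of analysis:

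- Two-tailed t tests, described as paired: "tests will be used to compare covariates and dependent variables from the infant groups". No covariates are attached.
- A one-way ANCOVA for the "effects of covariates (sociodemographic and neonatal intensive care unit hospitalization variables, postpartum depression, and posttraumatic stress) on the comparisons between groups" and between visits. Centre, pregnancy type and Kangaroo Care are not named.
- An open list: "Other statistical techniques such as matching, odds ratios, and logistic regression will also be used". No covariates or matching variables are given.

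Study Limitations adds that the two infants of a twin pair always go to the same arm. The Statistical Analysis section names no method for that clustering.

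**The concern.** Stratified blocks make the arms alike on the stratification factors. The treatment difference then varies less from one randomisation to another than it would under simple randomisation. A linear analysis that leaves the factors out does not know this: their variance stays in the residual, the reported standard error is too large, and the precision that the design bought is not used.

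The article does not simply stay silent on covariates. It lists groups of them, and two of these groups, depression and posttraumatic stress, are measured at 2, 6 and 12 months, after allocation. The baseline factors that defined the allocation are not in the list. At stake are over-wide intervals and a test that rejects too rarely, to a degree set by how prognostic the strata are.

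**Working it through.** **Inputs from the article.** Three stratification factors and blocks of four (Protocol section); 55 infants per group, 110 in total (Study Design); two-sided alpha taken as 0.05, and power 0.80 (Sample Size); twin pairs allocated together (Study Limitations).

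**Inputs assumed.** R2, the share of outcome variance explained by the strata, is not given; 0 to 0.30 is used. The share of twin infants (0 to 40%) and the within-pair correlation (0.3 to 0.6) are not given either.

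**The plan's own figure.** The article gives none for this point. Its sample size, 23 per group for 57% v 13%, is closely reproduced: 22 with a continuity-corrected two-proportion formula or with Fisher's exact test. This point does not change that figure.

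**Step 1: standard error.** With the arms balanced on the strata, the true variance of the difference is (1 - R2) times the variance that the unadjusted model reports. So reported SE / true SE = 1/sqrt(1 - R2).

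**Step 2: type I error.** The unadjusted test rejects when the estimate exceeds 1.96 reported SEs, which is 1.96/sqrt(1 - R2) true SEs. Type I error = 2 x [1 - Phi(1.96/sqrt(1 - R2))].

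**Step 3: lost power.** The true SE is the same with or without adjustment; only the threshold is too high. For 80% power the adjusted test needs a difference of 0.84 + 1.96 = 2.80 true SEs. The unadjusted test needs 0.84 + 1.96/sqrt(1 - R2). The true SE falls with sqrt(n), so the equivalent increase in infants is [(0.84 + 1.96/sqrt(1 - R2))/2.80]^2 - 1. At a difference that gives the adjusted test 80% power, unadjusted power is Phi(2.80 - 1.96/sqrt(1 - R2)).

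| R2 | SE too large by | 1.96/sqrt(1 - R2) | Type I error | Unadjusted power (adjusted 80%) | Equivalent extra infants |
|---|---|---|---|---|---|
| 0 | 0% | 1.96 | 5.0% | 80% | 0% |
| 0.05 | 3% | 2.01 | 4.4% | 78.5% | 4% |
| 0.10 | 5% | 2.07 | 3.9% | 76.9% | 8% |
| 0.20 | 12% | 2.19 | 2.8% | 72.9% | 17% |

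**Step 4: check by simulation.** Stratified blocks of four were simulated for 110 infants with a continuous outcome, three equally likely centre/Kangaroo cells carrying the stratum effect, no twins, and 2,500 runs per setting (simulation error about 0.4 points for type I error, 0.8 for power).

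| R2 | Type I, strata out | Type I, strata in | Power at 0.5 SD, out | Power at 0.5 SD, in |
|---|---|---|---|---|
| 0.05 | 3.7% | 4.2% | 75.5% | 77.2% |
| 0.10 | 3.7% | 5.0% | 74.8% | 78.2% |
| 0.20 | 3.1% | 5.0% | 78.0% | 84.0% |
| 0.30 | 2.5% | 5.2% | 79.0% | 88.2% |

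At R2 = 0.20 the true SE was 0.170 either way, while the unadjusted model reported 0.190. Direction and rough size agree with the formula.

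**Step 5: twins.** With 40% twin infants and within-pair correlation 0.6, type I error was:

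| R2 | Strata out | Strata in | Strata in, family-clustered SE |
|---|---|---|---|
| 0 | 7.6% | 7.8% | 5.4% |
| 0.20 | 5.2% | 7.5% | 5.1% |

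Twin clustering makes the reported SE too small. In the second row the two errors roughly cancel when the strata are left out, and adding the strata alone exposes the clustering. Both parts of the remedy are needed.

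**The case against.** The strongest reply is that a one-paragraph summary in an article is not a model specification. It names classes of covariates, "sociodemographic and neonatal intensive care unit hospitalization variables, postpartum depression, and posttraumatic stress", and sociodemographic variables may carry part of the centre contrast, while hospitalisation variables, which include skin-to-skin contact, may carry part of Kangaroo Care. Matching and logistic regression are left open, and a paired test on infants matched within strata would absorb the strata. A fuller analysis plan may exist. This stands in part: a reader might infer that the strata are excluded, and the article does not say so. But the list is stated, none of its groups plainly covers pregnancy type, no matching variables are named, and nothing commits the analysis to any of the three factors.

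Other stronger readings are also unsupported:

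- **That the results would be biased or give too many false positives.** Leaving out the strata biases nothing, and by itself makes the test conservative.
- **That the trial's tests will therefore be conservative overall.** Twin clustering works the other way. The twin share and correlation are not given, so the net direction is unknown.
- **That adjustment is worth 1/(1 - R2) in infants, that is 5%, 11% and 25%.** This treats the unadjusted estimate as if it had the full unstratified variance. Stratification has already reduced that variance, so the gain is the smaller one in Step 3.
- **That the loss falls on a trial already short of power.** On the article's own rates about 23 per group suffice, against 55 planned. Whether those rates, or the stated effect size of 0.25, are sound is a separate question.
- **That the loss must be material because district poverty differs.** Poverty rates are not outcome differences, and the article gives no R2.

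**Conclusion.** The point holds in a limited form. The design stratifies on three factors and the stated analysis does not name them. For the linear model, if the strata are prognostic and twin clustering is set aside, the reported standard error is too large by about 3%, 5% and 12% at assumed R2 of 0.05, 0.10 and 0.20. Those are assumptions, not figures from the article, and so is the resulting size: a loss of about 1.5, 3 and 7 points from 80% power. The figures do not carry over directly to logistic regression, where adjustment also changes the odds ratio being estimated. The omission costs efficiency rather than validity, and it is worth correcting because correction is cheap.

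**What to change.** In the Statistical Analysis section, or in the analysis plan if there is one:

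1. Include the stratification factors as fixed effects in the primary between-group model. Kangaroo Care exists at one centre only, so code centre and Kangaroo Care as one three-level factor (private centre; public centre with Kangaroo Care; public centre without), and add single or twin pregnancy.
2. Account for twin pairs with family-clustered standard errors or a family random effect. The twin covariate alone does not do this.
3. If a logistic model is used, state that the odds ratio adjusted for these factors is the target.

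The cost is three model parameters (two for the three-level factor, one for pregnancy type) and the change of estimand in the logistic model. The strata are already recorded for randomisation, so no new data, visits or infants are needed. The wording should be settled before the groups are compared.
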